### **13.2. Estimation of possible loss**

In order to minimize the sample loss throughout the study, we have adopted several measures aimed at maintaining motivation and reinforcing the participation of the participants: the members of the control group will sign an agreement to carry out the relevant evaluations to formalize the reservation of their place in the second promotion of the course. Once the study is completed, participants will be rewarded with an ECTS credit of free configuration (approved by the UCM Studies Commission on November 12, 2020) and object of academic recognition for the degree in medicine. In addition, participants who complete all evaluations of the study will receive a gift book on the theme of the program. For all the above, we expect a sample loss of less than 5%.

### **13.4. Description of recruitment and requirements of participants**

The CCT® program will be offered to all students of the Faculty of Medicine of the UCM enrolled in the 2020-21 academic year. This offer will be made through the Vice-rectorate of students of the Faculty of Medicine of the UCM, the dissemination screens of the library, the association of students of said faculty and course delegates. The selection of the participants in the study will be made among those students who apply for enrollment in the CCT® program. In the selection, preference will be given to those students who are in the 3rd-6th year of training because it is the period in which they are in contact with patients in the different hospitals associated with the UCM.

Study inclusion criteria include: 1) being of legal age; 2) sufficient level of Spanish to understand the instructions and sessions of the program; 3) be enrolled in the Faculty of Medicine of the UCM during the academic year 2020-21; (4) commitment to attend the entire programme; 5) provide informed consent to participate in the study; and 6) have access to the internet and computer to be able to carry out the online sessions.

Exclusion criteria include: (1) having a severe mental disorder in the active phase; 2) be under the influence of alcohol or other substances during the evaluation of the criteria or the sessions of the program; and 3) participate in another standardized meditation program during the course of the program.

The criterion of attendance at 75% of the sessions of the program will be used as an indication of "minimal exposure to treatment".

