### **8.1.4. Compassion in medical studies**

Some studies demonstrate a decrease in empathy and compassion during medical school and residency (Hojat, 2004; Bellini, 2005; Stepien, 2006; Neumann, 2011), especially in the transition to contact with patients (Hojat, 2009b; Neumann, 2011; Wilson, 2012). Other data indicate that medical students start the career in better mental health conditions than individuals of the same age enrolled in other careers, deducing that medical studies contribute to the deterioration of the mental health of students (Brazeau, 2014).

However, compassion is not a primary goal of career teaching even though the compassion of health professionals can be improved with training (Hojat, 2004; Stepien, 2006; Kelm, 2014).

Institutions such as the American Association of Medical Colleges or the American Medical Association are underscoring the importance of compassionate patient care (AAMC; Kelm, 2014). This belief is supported by recent publications (Patel, 2019) and studies conducted with medical students in which it is concluded that: i) compassion training can be an effective and attractive option to reduce burnout and, at the same time, promote the well-being of students and improve their interactions with patients; and ii) teachers should consider offering these skills to students as it appears to reduce empathic erosion suffered by students more directly than stress management training in isolation (Weingartner, 2019).

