#### **9. DESIGN**

A randomized, controlled, unicentric trial will be conducted with a control group on the waiting list (parallel groups). A 1:1 randomization will be performed (using the relevant function in Excell), with a single-blind masking. The simple blind is guaranteed by the division of weights in the research team, so that the person in charge of the evaluation and analysis of data does not participate and is blind to the process of randomization and the formation of the groups (RP). The IP of the project (BR) will be in charge of summoning the participants and assigning the groups.

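### Minor, cheap improvement: balance the allocation of 44 students on clinical stage (years 1-2 v years 3-6), which the protocol itself singles out

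*Protocol*

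**What the plan says.** **Who can enter.** Protocol Section 13.4 states that the "program will be offered to all students of the Faculty of Medicine of the UCM". The only inclusion criterion touching on study stage is to "be enrolled in the Faculty of Medicine of the UCM during the academic year 2020-21". Year of training enters as a selection rule: "preference will be given to those students who are in the 3rd-6th year of training", and the reason given is "because it is the period in which they are in contact with patients in the different hospitals associated with the UCM".

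**Why stage might matter.** The background in Section 8.1.4 reports that "Some studies demonstrate a decrease in empathy and compassion during medical school and residency", "especially in the transition to contact with patients". Section 12 lists compassion among the main variables and empathy among the secondary ones.

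**How students are allocated.** Section 9 says: "A 1:1 randomization will be performed (using the relevant function in Excell), with a single-blind masking". It names no stratification, blocking or minimisation. Section 9.1 places allocation after the baseline assessment. Section 13.1 sets the total at 44, with 22 per group.

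**How the data are analysed.** Section 14 uses group and time as the two factors of the main mixed ANOVA. It adds ANCOVAs with the baseline as covariate and tests baseline differences with t and chi-square tests. Year of training is not named in any of these.

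**The concern.** The protocol picks out one student characteristic as important enough to steer selection. Its own literature review connects that characteristic with two of the outcomes. It then leaves the characteristic to chance in a sample of 44.

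Year of training is used for selection, so it is known before anyone is allocated. Balancing on it needs no extra data.

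Adjusting for the baseline score deals with a difference in starting level between early-year and clinical students. It would not fully remove a difference in how much the two groups change during the trial, if there is one. In that case, an uneven split of early-year students between arms moves the estimated programme effect in this one trial. At stake is some avoidable noise in the arm difference, mainly for compassion and empathy.

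**Working it through.** **Inputs from the protocol**
- Total 44, 22 per arm (Section 13.1).
- 1:1 allocation without balancing factors (Section 9).
- Years 1-2 eligible (Section 13.4).

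**Assumed, not in the protocol**
- Number K of early-year students among the 44: varied from 4 to 22, with K = 12 as the worked case.
- Difference g between stages in mean change: 0.25, 0.5 and 0.8 SD.
- Arms exactly 22 and 22.

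**The plan's own figure.** N = 44 can be reproduced as a between-groups repeated-measures test with f = 0.40, 4 measurements and an assumed correlation of 0.5. The noncentrality is 0.40² × 44 × 4 / (1 + 3 × 0.5) = 11.26, with 1 and 42 degrees of freedom, and power is 0.906. Section 13.1 states neither the effect metric nor the correlation. The total serves here only as an input.

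**Step 1: chance of an uneven split.** Let x be the number of early-year students in one arm. It is hypergeometric: P(x) = C(K, x) · C(44 − K, 22 − x) / C(44, 22).
- For K = 12, P(0) to P(4) are 0.0000, 0.0007, 0.0071, 0.0363 and 0.1109, which sum to 0.155. Doubling for either direction gives **0.31** for 8:4 or worse.
- For K = 11, the same calculation for 8:3 or worse gives **0.16**.

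**Step 2: dependence on K.** The arm difference in the share of early-year students is |2x − K| / 22. Its root mean square is (2/22) × √[22 × (K/44) × (1 − K/44) × 22/43].

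| K of 44 | P(10 points or more) | P(20 points or more) | Root mean square, points |
|---|---|---|---|
| 4 | 0.11 | 0 | 8.8 |
| 7 | 0.41 | 0.095 | 11.2 |
| 9 | 0.46 | 0.13 | 12.3 |
| 11 | 0.49 | 0.16 | 13.2 |
| 12 | 0.31 | 0.09 | 13.6 |
| 13 | 0.51 | 0.19 | 13.9 |
| 22 | 0.37 | 0.13 | 15.2 |

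The probabilities jump between odd and even K because only whole students can differ. The last column is smooth.

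**Step 3: effect on the arm difference.** Shift = (difference in shares) × g. At 8:4 the shares are 8/22 = 36% and 4/22 = 18%, a difference of 4/22. The standard error of a difference between two means with 22 per arm is √(2/22) = 0.30 SD.

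| g (SD) | Shift (SD) | Shift / SE | Type I error given this split |
|---|---|---|---|
| 0.25 | 0.045 | 0.15 | 5.3% |
| 0.5 | 0.091 | 0.30 | 6.0% |
| 0.8 | 0.145 | 0.48 | 7.7% |

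The last column is Φ(−1.96 − b) + Φ(−1.96 + b), with b = shift / SE. Averaged over all splits for K = 12, the root-mean-square shift at g = 0.5 is 0.136 × 0.5 = 0.07 SD.

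**Step 4: after stratifying.** With each stratum split in half, the arms differ by at most one early-year student, or 1/22 = 4.5 points. At g = 0.5 the shift is at most 0.5/22 = 0.02 SD. The total stays at 44.

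**The case against.** **Unstratified randomisation is valid.** This stands. The imbalance is a matter of chance, the type I error averaged over randomisations remains 5%, and the ordinary standard error already allows for it. A reader might infer that stage is confounded with arm in the sense of a bias built into the design. The documents do not support that.

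**The background is not a statement about this trial.** This also stands. A reader might infer that the protocol says years 1-2 and years 3-6 follow different courses. Section 8.1.4 reports only that some studies found a decline across medical school and residency. It gives no size and says nothing about divergence over an 8-week programme or a 6-month follow-up. A stage difference in change is therefore an assumption.

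**No claim about students in patient contact is at risk.** Section 13.4 might suggest that the trial's conclusion is meant for such students. The title, the first hypothesis (8.4) and the main objective (10) all concern medical students of the university, so admitting all years fits the target.

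**The reach is narrow.** Compassion is one of four groups of main variables, and the sample size was set on emotional distress, for which the protocol describes no stage effect. The proposed strata are also coarse: years 3-6 pool students just entering patient contact with those well past it.

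**Other parts of the plan may cover it.** The preference for years 3-6 works against a large early-year share. A SAP, not shown, could add stage as a covariate, which would also remove the shift. The allocation method, however, belongs in the protocol, and Section 9 fixes it without balancing. The baseline tests lead to no stated action.

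**Conclusion.** The point holds as a minor improvement and not as an error. Years 1-2 are eligible, stage is known before allocation, the protocol's own background makes it a plausible predictor of compassion and empathy, and allocation ignores it.

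Under the assumed 12 early-year students and 22 per arm, a split of 8:4 or worse has probability 0.31. With an assumed 0.5 SD stage difference in change, that split moves the arm difference by about 0.09 SD, or about 0.3 standard errors. The size depends on inputs that the documents do not give. With 4 early-year students a 20-point imbalance cannot occur, and with none there is nothing to balance. The case for acting is that the remedy costs almost nothing, not that the expected harm is large.

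**What to change.** In Section 9, state that after the baseline assessment students are randomised 1:1 within two strata, years 1-2 and years 3-6. In the allocation sheet, give each student a random number, sort by it within each stratum and split each stratum in half. If both strata have an odd number of students, assign the two odd places to opposite arms so that the totals stay 22 and 22. In Section 14, include the stratum as a factor in the between-group analysis.

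The cost is one extra sort, one model term and one degree of freedom, with a possible one-person imbalance per stratum. The sample size does not change. If all places go to years 3-6, only one stratum exists and the step changes nothing.

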#### **14. STATISTICAL ANALYSIS**

Following the CONSORT recommendations, Intention-To-Treat Analysis will be performed to handle lost data. A diagnosis of the randomness pattern of the loss will begin using Little's MCAR test. The baseline differences between completers (i.e., per-protocol) and missing will also be analyzed to determine if there are any variables in the dataset that predict data loss. Depending on the loss pattern, multiple imputations will be made or by means of Maximum Likelihood algorithms. Finally, sensitivity analyses will be performed comparing the per-protocol data with the imputed ones to determine if the imputation has generated biased estimates. As indicated in the previous section, the criterion of attendance at 75% of the sessions of the program will be used as an indicator of "minimal exposure to treatment".

Student's t-tests and chi-square tests will be used to analyze differences between groups at baseline. The main analysis will be a mixed ANOVA with two factors: independent measures group factor (experimental vs control) and repeated measures time factor (pre, post, follow-up 2 and 6 months). ANCOVAs will also be performed using baseline as a covariate in analyses and repeated measure ANOVAs to assess the maintenance of changes over time. The analysis of variance will be complemented by mediating and moderating analyses to study the mechanisms of change of the program. A significance

level of alpha 0.05 will be defined in bilateral contrasts. Statistical analyses will be carried out using SPSS (v. 25) and R (v. 3.6.1) software.

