### **11.2 Program Details**

The CCT® program consists of 6 steps that are developed in eight weeks. Specifically:

*Week 1. Settlement and approach*

Development of mindfulness, settling the mind on the present experience with acceptance and without judgment through exercises aimed at focusing attention on the breath by loving, with kindness, attention back whenever it is distracted.

*Week 2. Compassion as a natural capacity*

Learn to recognize the physical and psychic signs associated with compassion through dialogue and guided exercises.

*Week 3. Self-pity*

It presents the idea that the cultivation of self-compassion is the basis for developing compassionate behavior towards others. Training in the practice of self-compassionate dialogue, self-acceptance and growth of these skills in difficult situations.

*Week 4. Self-love*

Learn to cultivate warmth, appreciation, joy and gratitude for oneself.

*Week 5. Shared humanity*

Recognition of shared humanity (seeing the other "just as I am") and interdependence as the foundation of compassion toward others.

*Week 6. Compassion*

From shared humanity and interdependence, cultivate compassion for all beings, including difficult ones.

*Week 7. Active compassion*

Aimed at developing inner stability to welcome the suffering of others and offer one's own happiness.

*Week 8. Integrated Compassion Cultivation Practice*

Bring together the elements of the previous steps into a compassionate meditation practice that can be followed as a daily practice

These six steps will be developed through:

- 8 weekly meetings of 2h online duration (due to COVID-19) consisting of relational exercises, meditations and dialogues on pedagogy and science related to the theme of the week. The online meetings will be held through the Zoom platform.
- Guided meditations recorded in audios of 20-30 min duration to be carried out daily (formal practices).
- Informal practices in everyday life

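### Comparing per-protocol with imputed results cannot show whether imputation is biased, so Section 14's stated sensitivity check does not answer its own question

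*Protocol*

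**What the plan says.** All the relevant rules are in Section 14 of the protocol, with one cross-reference to Section 13.4.

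- Overall strategy: "Intention-To-Treat Analysis will be performed to handle lost data".
- Diagnosis, first step: "A diagnosis of the randomness pattern of the loss will begin using Little's MCAR test".
- Diagnosis, second step: "The baseline differences between completers (i.e., per-protocol) and missing will also be analyzed", in order to find variables that predict loss. This is the only place where per-protocol is given a meaning, and that meaning is completers.
- Choice of method: "Depending on the loss pattern, multiple imputations will be made or by means of Maximum Likelihood algorithms".
- Sensitivity analysis and its purpose: "sensitivity analyses will be performed comparing the per-protocol data with the imputed ones to determine if the imputation has generated biased estimates".
- Directly after that, the section recalls that "the criterion of attendance at 75% of the sessions of the program will be used as an indicator of" minimal exposure to treatment. Section 13.4 states the same criterion.

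Section 13.2 expects a sample loss of less than 5%, and Section 13.1 plans 44 participants, 22 per group.

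**The concern.** The protocol states a criterion for imputation bias, and the criterion is not valid. An estimate can only be shown to be biased against a reference that is itself unbiased for the same quantity. Neither completers nor good attenders form such a reference for the comparison of all randomised participants. Both sets are defined by what happens after allocation.

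The check can therefore mislead in two directions. Agreement may only mean that both estimates share a bias. A gap may only mean that a different, selected population was analysed. A reader of the trial report could be reassured or alarmed about the main result for the wrong reason.

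The method rule has a related weakness. Multiple imputation and maximum likelihood, in their standard forms, both assume missing at random. Whatever the diagnosis shows, it does not favour one over the other, and it cannot exclude missing not at random.

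**Working it through.** **Inputs from the protocol.** N = 44, 22 per group (Section 13.1); loss below 5% (Section 13.2); eight sessions (Section 11.2), so 75% attendance is 0.75 × 8 = 6 sessions; waiting-list control without sessions in phase 1 (Section 9.1). Expected loss is at most 44 × 0.05 = 2.2, about 2 participants.

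**Reading A: per-protocol means attenders.** Let p be the share of the CCT arm below 75% attendance and g the amount by which they score worse than attenders. The full-arm mean is the attender mean minus p × g, so dropping non-attenders shifts the CCT mean by p × g even when no data are missing. The protocol gives neither p nor g; the values below are assumptions.

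| p | g = 0.25 SD | g = 0.5 SD |
|---|---|---|
| 10% | 0.025 | 0.05 |
| 20% | 0.05 | 0.10 |
| 30% | 0.075 | 0.15 |

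**Simulation of both readings.** Pre/post data, N = 44, 4000 replicates per scenario, ANCOVA on baseline. Assumed: true effect −0.80 SD (negative favours CCT), pre-post correlation 0.6, about 19% of the CCT arm below 75% attendance with poorer prognosis, and the strength of each loss mechanism. Complete-case ANCOVA stands in for multiple imputation or maximum likelihood (MI/ML), because with a fully observed baseline it gives the same missing-at-random estimate. The MI/ML column is therefore also the completer estimate.

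| Loss | Mechanism | Full data | MI/ML (= completers) | Bias of MI/ML | 75% attenders | Attenders minus MI/ML |
|---|---|---|---|---|---|---|
| 5% | MCAR | −0.796 | −0.796 | 0.000 | −0.890 | −0.094 |
| 5% | MAR | −0.793 | −0.792 | 0.001 | −0.886 | −0.094 |
| 5% | MNAR | −0.792 | −0.758 | 0.034 | −0.848 | −0.090 |
| 10% | MCAR | −0.796 | −0.796 | 0.000 | −0.887 | −0.091 |
| 10% | MAR | −0.801 | −0.799 | 0.002 | −0.890 | −0.091 |
| 10% | MNAR | −0.803 | −0.740 | 0.063 | −0.825 | −0.085 |
| 20% | MCAR | −0.803 | −0.805 | −0.002 | −0.897 | −0.092 |
| 20% | MAR | −0.798 | −0.799 | −0.001 | −0.889 | −0.090 |
| 20% | MNAR | −0.798 | −0.701 | 0.097 | −0.781 | −0.080 |

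(MCAR: missing completely at random; MAR: missing at random; MNAR: missing not at random.)

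- Under reading A the planned comparison shows a gap of 0.08 to 0.09 SD in every row, while the true bias of the imputed estimate runs from zero to about 0.10 SD. The gap is smallest where the bias is largest.
- **Reading B: per-protocol means completers.** The compared estimates coincide in this pre/post setting, so the gap is zero in every row, including those with bias of 0.034, 0.063 and 0.097 SD. With the 2- and 6-month visits the two could differ, but a difference would still not show which one was biased.

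**Little's test.** In the same simulation, among samples with any loss, it rejects in 45% (MAR) and 17% (MNAR) at 5% loss, and in 90% and 41% at 20% loss. A rejection does not separate MAR from MNAR, so it cannot guide the choice of method.

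**Size of a delta analysis at the expected loss.** Shift in the CCT mean = (missing in CCT ÷ 22) × delta. With delta 0.5 SD: 1/22 × 0.5 = 0.023 SD if one loss falls in that arm, and 2/22 × 0.5 = 0.045 SD if both do. With delta 0.25 SD: 0.011 and 0.023 SD.

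**The case against.** The best defence is that this is only a supporting analysis and the stakes are small. Analysis of all randomised participants remains the plan, loss is expected to be about 2 of 44, and naming one imputation method is the kind of detail a statistical analysis plan may supply. A large gap at very low loss would also be a fair prompt to recheck the imputation model. All of this stands and limits the weight of the point. It does not rescue the criterion: the protocol says that the comparison will determine bias, which is a wrong stated rule and not a missing detail.

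Four stronger readings are tempting, and the document does not support them.

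- That per-protocol is defined by 75% attendance. Section 14 equates it only with completers. The attendance sentence follows directly and makes the text ambiguous, but the link is an inference. Attendance is one-sided only in phase 1, since the waiting list is later offered the programme. Section 13.4 also requires a commitment to attend the whole programme, so non-attendance may be low.
- That Little's test picks the method. It only begins a diagnosis that also looks for baseline predictors of loss, which is useful for choosing imputation variables.
- That the test has almost no power here. The simulated 45% rejection under strong MAR at 5% loss does not bear that out.
- That a correct intention-to-treat result could be set aside for a more favourable attenders-only estimate. No text allows this.

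**Conclusion.** The point holds in limited form. The comparison specified in Section 14 cannot determine whether imputation is biased under either meaning of per-protocol. Under the completer meaning its agreement can hide a shared bias; under the attendance meaning it can show a gap without any imputation error. The 0.10 SD example, the 0.025 to 0.15 SD range and the simulation all rest on assumed inputs, but the logical failure does not depend on them.

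Making the choice between multiple imputation and maximum likelihood depend on the loss pattern has no statistical basis, but should have little numerical effect because both rest on the same assumption. If loss stays below 5%, the practical consequence of lost data is small, and it grows with higher loss. Non-attendance is a separate matter that the 5% does not bound. Correction is worthwhile and cheap, but the main analysis is not undermined.

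**What to change.** In Section 14:

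1. Name one method valid under missing at random, either a likelihood-based model or multiple imputation, for all randomised participants as allocated, and remove its dependence on the loss pattern.
2. Keep the search for baseline predictors of loss only to choose imputation or auxiliary variables. Little's test may be reported, but should decide nothing.
3. Replace the per-protocol comparison, as the test of imputation bias, with a delta-adjusted sensitivity analysis, for example with missing CCT outcomes made 0.25 and 0.5 SD worse in the unfavourable direction of each scale. This does not prove or exclude bias; it shows how far the conclusion depends on the missing-at-random assumption.
4. State whether per-protocol means completers or 75% attenders, and report any such analysis separately and labelled as what it is.

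The cost is a few sentences and one small extra analysis, with no change to data collection or sample size.

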#### **8.4. Hypothesis**

1. The standardized Compassion Cultivation Training (CCT) program will produce an improvement in emotional well-being and a reduction in psychological distress (stress, anxiety, depression) and burnout of post-program medical students compared to a control group on the waiting list.
2. Such changes shall be maintained over time two and six months after the end of the programme.
3. The above changes will be driven by increases in compassion for oneself, compassion for others, attention to the present moment, and emotional regulation skills.
4. The skills developed in the program will be a protective factor for the management of stress and psychological distress caused by the COVID-19 pandemic.

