### **Secondary objectives**

- 1) Examine whether the changes produced by the program are maintained two and six months after the end of the program.
- 2) Examine changes in psychological mechanisms mediating positive program outcomes. To assess whether compassion training is a protective factor against the stress and psychological distress caused by the COVID-19 pandemic.

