## **13. STUDY POPULATION AND TOTAL NUMBER OF PATIENTS**

### **13. 1. Sample calculation method**

The sample size was determined a priori using the G\*Power software (v. 3.0.10). The sample size required to analyze a mixed ANOVA (the group factor as an independent measure and the time factor as a related measure), with an expected effect size of 0.40 (Brito-Pons et al., 2018), a significance level of 0.05, and a power of 90%, the estimated sample size is 44 participants in the entire sample (22 in each group). This estimation of the sample size has been carried out for the pre-post change in the variable of emotional distress (i.e., stress, anxiety and depression).

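### Maintenance of the effect is assigned to repeated-measures ANOVA, which can count against retention but cannot establish it; with 22 trained participants, loss of half the benefit would often be non-significant

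*Protocol*

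**What the plan says.** Hypothesis 2 (Protocol Section 8.4) reads: "Such changes shall be maintained over time two and six months after the end of the programme". The first secondary objective (Section 10) is: "Examine whether the changes produced by the program are maintained two and six months after the end of the program".

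Section 14 names the method for this question: "repeated measure ANOVAs to assess the maintenance of changes over time". It gives no margin, retained share or decision rule. The same section makes the main analysis a group-by-time mixed ANOVA with a "repeated measures time factor (pre, post, follow-up 2 and 6 months"), and adds that "ANCOVAs will also be performed using baseline as a covariate in analyses". The error rate is set by "level of alpha 0.05 will be defined in bilateral contrasts".

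Section 13.1 arrives at 44 participants, 22 per group, "with an expected effect size of 0.40", "a significance level of 0.05, and a power of 90" per cent. It ties that size to the pre-post change in emotional distress and does not say whether 0.40 is Cohen's f or d. Section 9.1 offers the waiting-list group the programme two months after the first course ends.

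**The concern.** Maintenance is a claim that little or nothing has been lost. Repeated-measures ANOVA tests the opposite null, that the means do not differ over time. If the post-programme and follow-up means differ significantly, maintenance is in doubt. If they do not, the result may reflect real persistence or simply too few participants to see a loss. A significant time effect across all four occasions says only that something changed at some point, which the initial improvement alone would produce.

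The sample size was set for a different question, the pre-post change. At stake is a stated hypothesis and a secondary objective: an imprecise null result after the programme could be reported as durability.

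**Working it through.** **Inputs from the protocol.** 22 per group, alpha 0.05 two-sided, power 90%, effect size 0.40 with no metric (Sections 13.1 and 14); expected loss below 5% (Section 13.2).

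**Assumptions, not in the protocol.** Between-occasion correlation rho of 0.5 to 0.7, with 0.3 as a wider check. Equal SDs on each occasion, with effects in SD units.

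**1. The plan's own figure.** For a between-factors test in a repeated-measures design, lambda = f²·N·m / (1 + (m−1)·rho). With f = 0.40, N = 44, m = 4 and rho = 0.5:

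lambda = 0.16 × 44 × 4 / 2.5 = 11.26, which on F(1, 42) gives power 0.906.

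N = 44 is therefore reproduced if 0.40 is f, which for two groups is a difference of about 2f = 0.8 SD. The pre-post interaction that Section 13.1 describes gives a different N at rho 0.5: 20 if 0.40 is f, and 68 if 0.40 is d (f = 0.20). Because the metric is unstated, both benefits, 0.8 SD and 0.4 SD, are carried forward.

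**2. Chance that a true loss is non-significant.** Paired post-to-follow-up test in the CCT arm, n = 22, 21 df:

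- SD of change = √(2(1−rho)): 1.000 at rho 0.5 and 0.775 at rho 0.7.
- Noncentrality = loss × √22 / SD of change. For a loss of 0.40 SD this is 1.876 at rho 0.5 and 2.422 at rho 0.7.
- Power from the noncentral t distribution; the chance of missing the loss is 1 − power.

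| True loss | Power, rho 0.5 | Power, rho 0.7 | Non-significant |
|---|---|---|---|
| 0.20 SD (half of 0.4) | 0.146 | 0.212 | 85% to 79% |
| 0.40 SD (half of 0.8, or all of 0.4) | 0.433 | 0.637 | 57% to 36% |
| 0.80 SD (all of 0.8) | 0.947 | 0.996 | 5% to 0.4% |

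At rho 0.3 the three chances of a non-significant result are 88%, 67% and 14%. With 21 participants (22 less about 5%) at rho 0.5 they are 86%, 59% and 6%. A three-occasion ANOVA over post, 2 and 6 months with linear decay (n = 22, rho 0.5) is weaker than the paired test. It misses a half loss 65% of the time (benefit 0.8 SD) or 88% (0.4 SD), and a full loss 9% or 65%.

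**3. Precision.** The 95% CI half-width for post-to-follow-up change is t(0.975, 21) × SD of change / √22. That is 2.080 × 1.000 / 4.690 = 0.44 SD at rho 0.5, and 0.34 SD at rho 0.7. It is about the size of half a 0.8 SD benefit, or most to all of a 0.4 SD benefit.

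**4. What the other planned tests add.** A pre-versus-follow-up contrast is significant only 5% of the time after full loss, so it guards against that case. But with half the benefit gone it is still significant 43% of the time (0.8 SD) or 15% (0.4 SD) at rho 0.5. It therefore detects remaining benefit and does not measure how much was kept. The between-group tests at 2 months have the same limit, though they do use the randomised comparison.

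**5. Power of an explicit retention rule.** Illustrative margin: lose no more than half the benefit, with true loss zero, one-sided 0.025, rho 0.5. With 22 participants the power is 43% if the benefit is 0.8 SD and 14% if it is 0.4 SD. Reaching 80% would need 52 and 199 CCT participants respectively.

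**The case against.** The strongest reply is that Section 14 contains no rule turning non-significance into maintenance. Contrasts and decision rules are often left to an analysis plan, and one may exist that is not shown. This stands. A reader might infer that the protocol commits the authors to calling a null result maintained, and the text does not support that. What the protocol does fix is the pairing of a no-loss claim with a test of no change, and nothing in it blocks the misreading.

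A reader might also infer that a non-significant change is the only route to a favourable statement, or that the analysis is confined to the CCT arm. Neither is stated. The time factor includes the pre-programme occasion, and the mixed ANOVA and ANCOVAs allow a between-group comparison at follow-up, so the 2-month randomised comparison is not discarded. These tests still show residual benefit and not retention. At 6 months the between-group comparison weakens, because controls who accept the offer in Section 9.1 are no longer untreated.

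A further tempting reading is that a benefit that has entirely gone would often pass as maintained. That holds only if the benefit is about 0.4 SD. Under the reading of 0.40 that reproduces N = 44, full loss is seldom missed.

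Finally, 22 may not be the number used. The protocol does not say whether waiting-list participants who later take the course would be pooled. With 44, power for a 0.40 SD loss would be 0.74 to 0.92 at rho 0.5 to 0.7. For a 0.20 SD loss it would be only 0.25 to 0.39, so the concern shrinks but remains if the benefit is small.

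**Conclusion.** The point holds in limited form. The method named for maintenance cannot establish it, and the remaining planned tests show at most that some benefit persists. With 22 CCT participants, loss of half the benefit would often go undetected under either reading of 0.40. Frequent failure to detect full loss is confined to the smaller benefit.

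The figures rest on the assumed correlation, equal SDs, the two readings of the effect size and no pooling with the second course. A secondary objective is affected, not the main comparison, so this should be changed but does not threaten the trial's primary question.

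**What to change.** In Section 14, replace the clause on maintenance with three statements:

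1. The 2-month statement rests on the baseline-adjusted between-group difference with its 95% CI, using control assessments made before the waiting-list group starts the programme.
2. The post-to-2-month and post-to-6-month changes in the CCT arm are reported with 95% CIs. A non-significant change is not evidence of maintenance. Maintenance is claimed only if the CI excludes a loss larger than a share of the post-programme effect that the sponsor sets in advance; otherwise the report says that maintenance was not established. The half-benefit share used above is only an example.
3. Six-month results are described as uncontrolled where controls have been offered and have taken the programme.

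The change needs wording only: no new data, visits or participants, and item 1 largely uses the ANCOVA already planned. It does not add power. At this size a finding that maintenance was not established is likely, even if the benefit has in fact lasted.
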